### Data analyses

Due to expected changes in feeding behaviour and intake over 18 months, group but not time effects will be examined at each time point, with the exception of growth. Primary analysis will be according to intention-to-treat principles. A generalised estimating equations analytical approach will be used to account for the clustering within assessment clinics, as well as to permit data to be included for those not completing all assessments (thus optimizing power). Success of randomisation will be considered based on a comparison of the two groups across a range of centre, child, and carer characteristics, against *a priori *defined meaningful differences. Any noted imbalances at baseline will be accounted for in multivariable logistic regression modelling, adjusting for their potential confounding effect on the impact of intervention on each outcome.

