## Methods

### Overall study design

NOURISH is a multi-site RCT to be conducted in Brisbane and Adelaide, Australia. A consecutive sample of first-time mothers with healthy term infants will be recruited from postnatal wards of major maternity hospitals in both cities. Assessments and intervention will commence when the infants are 4-7 months old and will be conducted at existing child health clinics. Randomisation is to be on an individual dyad basis, stratified by assessment clinic. Follow-up will be for 18 months to 22-25 months of age. The intervention comprises two consecutive modules, each with six fortnightly group sessions, followed by monthly maintenance contacts for six months. Controls will have self-directed access to services at child health clinics. These are similar in both cities and may include growth measurements, written and web-based materials, a telephone help line and, in some cases, individual appointments (limited due to staff availability).

Funding for this first phase is from the National Health and Medical Research Council (Grant No 426704). Further funding is being sought to extend follow-up to five years to assess sustainability of impact on modifiable determinants of eating behaviour and to add outcome evaluation of effect at five years of age on weight status and other nutritionally-related outcomes (e.g. oral health). Ethical approval to conduct the study has been obtained from eleven Human Research Ethics Committees across both sites (Queensland University Technology HREC 00171 Protocol 0700000752.)

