### Allocation

On receipt of signed consent and completion of baseline assessment, participants will be randomly allocated to intervention or control according to a permuted-blocks randomisation schedule generated by the Institute's Research Methods Group, which includes this study's statistician, all of whom will otherwise not be involved in data collection or intervention delivery. Block sizes of four within strata defined by location of assessment clinic will be generated. Participants will be notified by mail of allocation and appropriate program schedules.

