### Intervention

#### Process

Fortnightly group sessions (n = 10-15 mothers/primary carers per group), will be delivered at existing child health clinics and co-led by a dietitian and psychologist with paediatric experience. Delivery through existing child health infrastructure will enhance cost effectiveness and relevance, build staff capacity, facilitate dissemination and translation of findings into practice and provide participants with convenient access in their local area. Onsite child care will be provided. Strategies to maintain intervention fidelity will include use of a standardised facilitator manual including protocols, procedures, activities and materials for each group session and standardised participant materials. Facilitators will meet regularly by teleconference with the study coordinators for session planning, review and supervision.

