### Sample size

Based on the number of eligible births in the target hospitals, a four month recruitment period and an overall baseline participation rate of 42% (60% Recruit 1, 70% Recruit 2) we aim to recruit 820 participants. Assuming a 65% completion rate, approximately 265 per intervention arm will available for the final analyses. There are no data published on the likely intra-cluster correlation coefficients (ICC) for the outcomes of our study, but we anticipate that they will be moderate given the (likely) greater demographic and socio-economic similarity within parents/carers attending the same clinic compared to those attending different clinics, and that the outcomes we are considering are associated with these characteristics [43]. A recent New Zealand study [43] reported a median ICC of 0.09 for nutrient outcomes obtained from 24-hour recall data in a cluster sample aged 1-14 years. In the absence of more direct data, we have assumed conservatively an ICC of 0.10 and, for an average cluster size of 20, we anticipate a design effect of the order of 2.9. Hence our sample size of 265 per group is effectively a sample size of 92 per group. For this, we shall be able to detect, with 80% power and type I error of 5% (two-tailed), meaningful clinical differences in prevalence of outcomes (indicator behaviours for positive feeding practices) as noted in Table 2.

**Table 2 T2:** Minimum meaningful differences between control and intervention groups, and those detectable with 80% power, 5% significance (two-tailed) for endpoint sample size of 265 per group, assuming a design effect of 2.9.

**Intake**	**Prevalence #**	**Detectable**	**Behaviour**	**Prevalence #**	**Detectable**
Fruit^a^	82 vs ≥ 95%^(iii)^	82 vs ≥ 95%	Offer new food >10 times^b^	28 vs ≥ 75%^(iii)^	28 vs ≥ 48%

Vegetable^a^	67 vs ≥ 95%^(iii)^	67 vs ≥ 84%	Refuses food- assume not hungry, take food away often/very often/always^b^	56 vs ≥ 84%^(i)^	56 vs ≥ 75%

Salty snacks^a^	27 vs ≤ 17%^(ii)^	27 vs ≤ 11%	Refuses food-offers no replacement food often/very often/always^b^	29 vs ≥ 44%^(i)^	29 vs ≥ 49%

Sweet beverages^a^	44 vs ≤ 28%^(ii)^	44 vs ≤ 25%	Use food as reward 'hardly ever'^b^	55 vs ≥ 83%^(i)^	55 vs ≥ 74%

Fried potato^b^	17 vs ≤ 8%^(i)^	17 vs ≤ 5%	Insist child eat 'hardly ever'^b^	46 vs ≥ 69%^(i)^	46 vs ≥ 66%

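### The planned GEE names the assessment clinic as its only cluster, although only the intervention arm is treated in shared groups; the 5% test is not secured if groups cross clinics or standard errors are model-based.

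*Protocol article*

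**What the plan says.** All places are in the protocol article.

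- **Overall study design:** "Randomisation is to be on an individual dyad basis, stratified by assessment clinic". **Allocation** adds: "Block sizes of four within strata defined by location of assessment clinic will be generated".
- **Intervention, Process:** "Fortnightly group sessions (n = 10-15 mothers/primary carers per group"), each co-led by a dietitian and a psychologist. The Abstract describes two modules of six sessions that combine education with peer support. Under Overall study design, controls find their own way to ordinary child health services, so they have no corresponding groups.
- **Sample size:** "we have assumed conservatively an ICC of 0.10". The reason given is that mothers at one clinic resemble each other socially and demographically. Detectable differences are stated "with 80% power and type I error of 5% (two-tailed").
- **Data analyses:** "A generalised estimating equations analytical approach will be used to account for the clustering within assessment clinics".

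The clinic is therefore the only source of clustering named in both the sample size and the analysis. The session group appears in neither. The article does not say whether a session group draws from one assessment clinic, whether groups stay together for Module 2, or whether GEE standard errors are robust or model-based.

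**The concern.** Because allocation is blocked within clinic, both arms are represented in each clinic. Similarity among mothers at the same clinic is then common to both arms and largely cancels from the arm comparison.

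Correlation produced by group treatment behaves differently. It arises after randomisation, in one arm only, from shared facilitators and peers, so it adds variance to the intervention mean that nothing in the control arm offsets. If the standard error does not contain that variance, confidence intervals are too narrow and the test rejects too often under the null.

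The planned design effect does not protect against this. It makes the sample larger than a simple calculation would require, which helps power, but it does not alter the standard error used in the final test.

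**Working it through.** **1. The plan's own figures.** "we aim to recruit 820 participants" and "Assuming a 65% completion rate, approximately 265 per intervention arm will available for the final analyses": 820 × 0.65 / 2 = 266.5, stated as about 265. Design effect with cluster size 20 and ICC 0.10: 1 + (20 − 1) × 0.10 = 2.9. Effective size: 265 / 2.9 = 91.4, or 266.5 / 2.9 = 91.9, stated as 92. These reproduce. They concern the clinic only.

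**2. Completers per session group.** 65% of 10-15 is 6.5 to 9.75, so 6.5-10 is used below.

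**3. Error rate if group correlation is left out of the standard error.** The session-group ICC (ρ) is assumed at 0.02, 0.05 and 0.10.

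- Intervention-arm design effect: DE = 1 + (m − 1)ρ
- Variance ratio for the arm difference, equal arms: R = (1 + DE) / 2
- True two-sided error: 2 × [1 − Φ(1.96 / √R)]

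| m | ρ | DE | R | True error |
|---|---|---|---|---|
| 6.5 | 0.02 | 1.11 | 1.055 | 5.6% |
| 6.5 | 0.05 | 1.275 | 1.137 | 6.6% |
| 6.5 | 0.10 | 1.55 | 1.275 | 8.3% |
| 10 | 0.02 | 1.18 | 1.09 | 6.1% |
| 10 | 0.05 | 1.45 | 1.225 | 7.7% |
| 10 | 0.10 | 1.90 | 1.45 | 10.4% |

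**4. When does a clinic-clustered GEE actually leave it out?** This was simulated under the null: continuous outcome, clinic ICC 0.10, 26 clinics, 260 per arm, groups of 10, 8,000 runs per scenario. The working correlation was taken as exchangeable, which is an assumption. In the crossing scenario, groups were formed without regard to clinic, the extreme case.

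| Groups and standard error | ρ = 0 | 0.02 | 0.05 | 0.10 |
|---|---|---|---|---|
| Within clinics, robust with t correction | 5.0% | 4.9% | 4.5% | 4.9% |
| Within clinics, robust with z | 6.7% | 6.5% | 6.1% | 6.2% |
| Within clinics, model-based | 5.1% | 6.1% | 7.4% | 10.8% |
| Crossing clinics, robust with t correction | 5.1% | 6.4% | 7.2% | 10.7% |
| Crossing clinics, model-based | 4.8% | 6.5% | 7.5% | 10.7% |

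The second row is above 5% but does not rise with ρ, so its excess comes from having few clusters, not from session groups. With 13 clinics the pattern is the same. Inflation due to the groups needs either crossing or model-based standard errors.

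**5. Does this call for more mothers?** With the clinic effect cancelling from the contrast and ρ = 0.10, the effective size per arm is 265 / 1.45 = 183 for m = 10. For m = 15, DE = 1 + 14 × 0.10 = 2.4, R = 1.70 and 265 / 1.70 = 156. Both exceed the planned 92.

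**The case against.** The strongest reply is that clustering on clinic may already absorb the session groups. A robust variance computed at a higher level covers any correlation nested below it, and the first row of the simulation confirms this.

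The article also makes nesting plausible. Assessments and sessions both take place at child health clinics, mothers are offered assessment sites near home (Recruit 2), and session venues are meant to be local (Process). The arithmetic fits. If the average cluster of 20 counts completers in both arms, 20 / 0.65 = 31 mothers are recruited per clinic, of whom about 15 are in the intervention arm: one group. If 20 is per arm, about 31 intervention mothers per clinic would form two or three groups.

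This much stands: a reader might infer that the plan ignores treatment groups outright and that its test must exceed 5%. The document does not support that. It does not state that groups cross clinics or that standard errors are model-based. Nor does it specify an exchangeable working correlation, or one fixed group with the same two facilitators through all twelve sessions.

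It can also be said that the variance estimator and the mapping of groups to clinics belong in a SAP. That is fair for those details taken alone. But the article does commit itself on which clustering the analysis handles, and it names the clinic only. Nesting remains an inference: mothers rank their preferred assessment venues, programme schedules follow after allocation, and nothing ties a session group to an assessment clinic.

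**Conclusion.** The concern holds in a conditional form. The stated analysis does not explicitly model a one-arm correlation that the intervention's design can create, and whether it is covered depends on two matters the article leaves open.

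- If groups cross assessment clinics, or standard errors are model-based, the real error of the nominal 5% test is about 5.6-6%, 6.6-8% and 8-10% at session-group ICCs of 0.02, 0.05 and 0.10.
- If groups are nested in clinics and the clinic-level variance is robust with a small-sample correction, the error stays near 5%.

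The range rests on assumed ICCs, on 6.5-10 completers per group, and on group correlation being wholly absent from the standard error. Partial crossing should give something in between. The finding concerns the validity of the test and the intervals, not the sample size.

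**What to change.** Record each intervention mother's assigned session group and state how groups map to assessment clinics. Then use a partially nested analysis:

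- GEE with the session group as the cluster in the intervention arm and each control dyad as its own cluster.
- Assessment clinic as a fixed stratum term.
- Robust variance with a small-sample correction.
- Mothers who stop attending stay in the group first assigned, in line with intention-to-treat.
- If mothers are regrouped for Module 2, the Time 3 analysis should account for that grouping.

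It would also help to report the session-group ICC, since none is available now. If all groups are confirmed to lie within one assessment clinic, a clinic-level robust variance with small-sample correction is an acceptable alternative.

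GEE keeps the marginal effect for binary outcomes, whereas a mixed logistic model would change it to a conditional one.

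The cost is small. Process evaluation already plans detailed attendance records, so the addition is one identifier and a different cluster variable. Intervals become slightly wider, and no larger sample is implied.

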### Measurements and procedures

#### Outcome measurements

Outcome variables are described in detail in Table 1 and along with covariates are to be measured by mother-completed questionnaires at baseline (Time 1, age 4-7 months) and six months after the completion of each 12-week intervention module at age 13-16 months (Time 2) and 22-25 months (Time 3). Questionnaires are to be completed at home and brought to assessment clinics where maternal and infant weight and height/length will be measured. Child intake will be measured at Times 2 and 3 using a telephone 24-hour recall conducted by a dietitian and a 2-day (one week and one weekend day) food record completed by the mother. Randomisation should optimise chances of no group difference in Time 1 infant intake which, along with maternal intake, will not be collected due to the resource and participant burden implications. Assessors will be trained and will not be involved in intervention delivery. Where a number of assessment tools are not suitable across all age groups, we have selected for age appropriateness within constructs, rather than consistency across time points.

**Table 1 T1:** Outcome measures for the study

**Participant**	**Measure - assessment sessions at child health clinics**	**T1**	**T2**	**T3**

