**Infant/Child**				

Food intake records H1	3 non-consecutive days (including weekend day), using 2 × 24 h food records + telephone 24 h-recall. Standard protocol (including estimation of breast milk intake and standardised visual aids for serve size estimation) will match FITS [48] and other [49] studies; well accepted in pilot study.		✓	✓

Food preference H2	The Wardle tool [37] adapted to Australian target foods. Mothers rate on 5-pt scale from 'likes a lot' - 'dislikes a lot' with option for 'hasn't tried it'	✓	✓	✓

Feeding behaviour H3	Children's Eating Behaviour Questionnaire [50]. Validated 35-item parent report of satiety responsiveness, fussiness, food responsiveness, enjoyment, emotional over/under eating.		✓	✓

Weight & growth	Recumbent length and weight. Weight, length and weight-for-length z-scores calculated using CDC EpiInfo (version 3.3.2).	✓	✓	✓

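### Covariate adjustment is triggered by baseline imbalance and named as logistic for every outcome, instead of being fixed in advance with the T1 values that are collected

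*Protocol article*

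**What the plan says.** The Data analyses section sets out three steps.

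- Main method: "A generalised estimating equations analytical approach will be used to account for the clustering within assessment clinics". Arms are compared at each time point without time effects, growth excepted.
- Baseline check: "Success of randomisation will be considered based on a comparison of the two groups across a range of centre, child, and carer characteristics", judged against meaningful differences defined beforehand. The characteristics are not named there.
- Adjustment: "Any noted imbalances at baseline will be accounted for in multivariable logistic regression modelling", applied to the intervention effect on every outcome.

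On what exists at baseline, the Outcome measurements section says in general terms: "Outcome variables are described in detail in Table 1 and along with covariates are to be measured by mother-completed questionnaires at baseline". Table 1 and the surrounding text are more specific.

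- Food preference ("The Wardle tool [37] adapted to Australian target foods"), growth and the parenting scales are ticked at T1, T2 and T3.
- The Infant Feeding Questionnaire is ticked at T1 and T2. At T3 the Child Feeding Questionnaire replaces it, because "we have selected for age appropriateness within constructs, rather than consistency across time points".
- The Children's Eating Behaviour Questionnaire is ticked at T2 and T3 only.
- Intake has no baseline by design: "Child intake will be measured at Times 2 and 3 using a telephone 24-hour recall", and "Randomisation should optimise chances of no group difference in Time 1 infant intake which, along with maternal intake, will not be collected".

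**The concern.** Under individual randomisation, a baseline difference between arms is chance. A rule that admits a covariate only when such a difference is noticed picks variables for the wrong reason. A strong predictor of outcome that happens to be balanced is left out, and a weak one that happens to differ is put in. The adjusted model is then unknown until the data are seen, and it may differ from what another analyst would fit, since the characteristics are not listed and the Covariates section offers many candidates.

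Two things follow. First, for outcomes with a T1 value, usually the best single predictor at hand, the stated rule uses that value only by accident of imbalance. Second, the rule names one model type for all outcomes. That suits the prevalences in Table 2, but not growth z-scores, parenting scales or questionnaire scores. At stake is power on the outcomes that have a T1 value, and clarity about which model will be reported.

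**Working it through.** **The plan's own figures (Sample size section).** Completers per arm: 820 × 0.65 / 2 = 266.5, stated as about 265. Design effect: 1 + (20 − 1) × 0.10 = 2.9. Effective size: 265 / 2.9 = 91.4, or 266.5 / 2.9 = 91.9, stated as 92. These reproduce. No baseline covariate enters that calculation.

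**Assumed input.** The correlation r between the T1 value and the follow-up value is not in the article. A range of 0.3 to 0.7 is used, with 0.2 added to show the low end. Clustering enters only through the effective 92 per arm.

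**Continuous outcome, formula.** The difference detectable with 80% power, unadjusted, is (1.960 + 0.842) × √(2/92) = 0.413 SD. Adjusting for a T1 value multiplies the variance by 1 − r², so power = Φ(2.802 / √(1 − r²) − 1.960).

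| r | variance factor | equivalent n per arm, 92/(1 − r²) | power, always adjusted |
|---|---|---|---|
| 0.2 | 0.96 | 95.8 | 81.6% |
| 0.3 | 0.91 | 101.1 | 83.6% |
| 0.5 | 0.75 | 122.7 | 89.9% |
| 0.7 | 0.51 | 180.4 | 97.5% |

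**Continuous outcome, simulation of the trigger** (one covariate, 92 per arm, 20,000 runs). The article does not give its thresholds, so two were assumed: adjust if the baseline difference has p < 0.05, or if the standardised difference exceeds 0.2.

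| r | power: unadjusted | trigger p < 0.05 | trigger > 0.2 SD | always adjusted |
|---|---|---|---|---|
| 0.3 | 79.6% | 80.0% | 80.5% | 83.0% |
| 0.5 | 79.1% | 80.3% | 82.2% | 89.3% |
| 0.7 | 79.2% | 81.2% | 85.2% | 97.3% |

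Type I error at r = 0.3, 0.5 and 0.7 was 4.9%, 4.1% and 3.6% under the first trigger, and 4.7%, 3.6% and 2.8% under the second. It was about 5% when always adjusted. The trigger is conservative, and it recovers only a small part of the available power.

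**Binary outcome, simulation** (46% against 66%, 6,000 runs, r on an underlying normal scale). Unadjusted power was 77% to 78%. Always adjusting gave 80%, 84% and 91%. The p < 0.05 trigger gave 77% to 79%. The standard error of the log odds ratio rises with adjustment (0.306 to 0.341 at r = 0.5), because the conditional log odds ratio is also larger (0.834 to 0.998). So the gain is in power, and the 1 − r² reduction must not be quoted for logistic models. This case is illustrative, since no same-measure T1 value is documented for the Table 2 outcomes.

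**Where the gain can apply.** Setting Table 1 against the rule, a same-measure T1 value exists for food preference, the parenting scales and growth at T2 and T3, and for the Infant Feeding Questionnaire at T2. None exists for intake (half of Table 2) or for the Children's Eating Behaviour Questionnaire. None is documented for feeding practices at T3.

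**The case against.** The strongest reply is that this is a condensed article, and covariate lists and link functions normally sit in a fuller document. The thresholds for imbalance are prospective, so the choice is not free. The outcomes that size the trial have no matching baseline, so the precision argument misses them. The correlations are assumed. T1 falls when solids are being introduced and the preference tool allows for foods not yet tried, so the correlation with preferences near age two could be close to zero.

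Much of that stands. The thresholds do limit discretion, the gain is confined to a subset of outcomes, and at r = 0.2 it is under two points of power. The Covariates section already names baseline feeding practices and maternal body mass index as covariates. Growth is excepted from the group-only comparison, so its T1 value may be used in a way the article does not describe. What does not stand is the appeal to missing detail: the article states a trigger and a model type, and both are poor choices as stated.

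A reader might also infer that the adjusted logistic model abandons the clinic clustering, or that scales will be dichotomised to fit it. The text says neither. A GEE with a logit link is itself a multivariable logistic model, so the wording is loose rather than wrong on clustering.

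**Conclusion.** The point holds in limited form. The stated rule selects covariates on chance imbalance, does not routinely use T1 values that are collected, and names a model type unsuited to continuous scores. For continuous outcomes with a T1 value, the forgone power is about 4, 10 and 17 points above 80% at assumed correlations of 0.3, 0.5 and 0.7, and almost nothing if the correlation is near zero. These figures rest on the plan's effective 92 per arm, and the trigger results on two assumed thresholds.

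Three stronger readings are tempting and not supported. A reader might infer that the rule inflates false positives; the simulation shows the opposite. A reader might infer that the primary model is data-driven; the article describes the primary analysis as intention-to-treat with GEE and does not say that the imbalance-adjusted model is primary. A reader might infer that the sample size is wrong or that the intake outcomes lose this precision; the sample size does not depend on this point, and intake has no T1 value to adjust for.

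**What to change.** Replace the imbalance trigger with a covariate set fixed before the data are seen, inside the clinic-clustered GEE.

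- Include arm, and the T1 value of the outcome wherever Table 1 shows one.
- For T3 feeding practices, use the T1 Infant Feeding Questionnaire as a proxy, expecting a smaller gain than from a same-measure baseline.
- For outcomes without a T1 value (intake and the Children's Eating Behaviour Questionnaire), name a few prognostic covariates already collected, such as maternal education and body mass index.
- Use an identity link for scores and z-scores and a logit link for the binary prevalences, and say that the clustering is retained in the adjusted model.
- Keep the baseline comparison descriptive, with imbalance-driven adjustment as a sensitivity analysis only.

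The cost is wording in the analysis plan. Every variable needed is already scheduled for collection.

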**Maternal**				

Feeding style and practices H3	The Infant Feeding Questionnaire [36]. 20-item - under/over-eating, hunger, infant cues, scheduling, use of food to calm.	✓	✓	
	Child Feeding Questionnaire [43] 28-item - 2-11 yrs. - feeding attitudes, practices, perceptions/concerns regarding weight.			✓

Parenting skills H4	Four brief scales from LSAC measuring warmth, irritability, consistency and overprotection (24 items)[41]	✓	✓	✓

BMI	Height and weight using standard procedures	✓	✓	✓

**T1 **= baseline, pre-allocation, infants 4-7 mths; **T2 **= mid study- 9 mths, infants aged 13-16 mths; **T3 **= final -18 mths, infants aged 22-29 mths. LSAC = Longitudinal Study of Australian Children

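### The baseline-imbalance adjustment names logistic regression for every outcome, but that model does not fit the z-scores, scale scores and 5-point ratings in Table 1

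*Protocol article*

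**What the plan says.** The Data analyses section of the protocol article sets out two steps.

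- **Main analysis.** "A generalised estimating equations analytical approach will be used to account for the clustering within assessment clinics", and also so that participants with incomplete assessments can be included. No link function or distribution is named.
- **Adjustment.** This step is conditional: "Any noted imbalances at baseline will be accounted for". The method the article then gives for it reads: "in multivariable logistic regression modelling, adjusting for their potential confounding effect on the impact of intervention on each outcome". No other adjusted model is mentioned.

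Table 1 lists outcomes of several types. Those that are not yes/no include:

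- growth: "Weight, length and weight-for-length z-scores calculated using CDC EpiInfo (version 3.3.2";
- child eating behaviour, labelled H3: "Validated 35-item parent report of satiety responsiveness, fussiness, food responsiveness, enjoyment, emotional over/under eating";
- food preference, labelled H2: "Mothers rate on 5-pt scale from 'likes a lot' - 'dislikes a lot";
- maternal feeding style and practices, labelled H3: a 20-item and a 28-item questionnaire;
- parenting skills, the only row labelled H4: "Four brief scales from LSAC measuring warmth, irritability, consistency and overprotection (24 items".

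The Sample size section, by contrast, is written for binary outcomes. It aims to detect "meaningful clinical differences in prevalence of outcomes (indicator behaviours for positive feeding practices) as noted in Table 2", and the statement below Table 2 about power for the primary outcomes refers to those prevalences.

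**The concern.** The adjustment sentence fixes both a model and its scope, and the two do not match. Logistic regression, as ordinarily understood, models a yes/no response. A z-score or a questionnaire scale score can enter it only after being cut at some value, and the article gives no cut-point for any of them. A 5-point rating would need either a cut or an ordinal extension that is not mentioned.

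Three things are at stake if the sentence is applied as written:

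- the adjusted results for growth, for the H3 questionnaires and for the only measure labelled H4 would depend on cut-points not fixed in this document;
- those results would be less precise than the collected data allow;
- the main and adjusted results for one outcome could be on different scales, such as a mean difference and an odds ratio, so a reader could not tell how much of any change came from the adjustment.

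**Working it through.** **1. Does the stated model fit each outcome type?**

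| Outcome (source) | Type | Logistic model fits as stated? |
|---|---|---|
| Food and behaviour prevalences (Table 2) | Yes/no | Yes |
| Weight, length, weight-for-length z-scores (Table 1) | Continuous | No |
| Eating-behaviour, feeding and parenting scales (Table 1) | Multi-item scores | No |
| Food preference ratings (Table 1) | 5-point ordered | Not without a cut or an ordinal form |

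**2. The plan's own effective sample size.** Inputs from the Sample size section: ICC 0.10, average cluster size 20, 265 per group at the end.

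- Design effect = 1 + (20 − 1) × 0.10 = 2.9, as stated.
- Effective size = 265 / 2.9 = 91.4; the article states 92.
- Check against Table 2: for 28% versus 48%, 92 per group, two-sided 5%, pooled-variance test without continuity correction, power is 80.3%. The stated figure is reproduced.

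The value 92 is used below.

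**3. What an uncut score could detect.** Detectable difference at 80% power = (1.960 + 0.842) × √(2/92) = 0.413 SD.

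**4. Information kept after a cut (illustration, assuming a normal score).** For a cut leaving a proportion p on one side, the fraction kept is φ(z_p)² / [p(1 − p)].

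| Cut | Kept | Lost |
|---|---|---|
| Median (50/50) | 0.637 | 36.3% |
| 20/80 | 0.490 | 51.0% |
| 10/90 | 0.342 | 65.8% |

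At a median split, 92 × 0.637 ≈ 59 per group of equivalent information.

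**5. Power after a cut, for the same 0.413 SD shift at 92 per group.**

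- Median split: 50% in one group becomes Φ(0.413) = 66.0% in the other. Power for 50% versus 66.0% is 59.7%, down from 80%.
- 20% cut: power is 53.9% if the shift raises the prevalence and 43.5% if it lowers it.
- Difference detectable with 80% power after a median split: 0.53 SD instead of 0.41 SD.

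The article supplies neither the cut-points nor the normality assumption. Both are mine, and the results do not carry over directly to 5-point ratings or skewed scores.

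**The case against.** The strongest reply is that this is loose wording in a condensed article. The power case rests on yes/no prevalences, so the authors may simply have named the model for their headline outcomes. The choice of link by outcome type is ordinary analysis-plan detail. The adjustment is also only triggered by a noted imbalance, in an individually randomised trial stratified by clinic.

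Much of this stands, and it rules out three stronger readings that a reader might infer.

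- **That the trial plans to dichotomise its scores.** It does not say so. No section mentions cutting a z-score or scale score, and the main GEE analysis names no link and can take continuous outcomes.
- **That the adjusted analysis drops the clinic-clustering correction.** A logistic model fitted by GEE is standard and is compatible with both statements. The article does not say that this is meant, but nothing in it says that clustering is abandoned.
- **That 36% to 66% of the information will be lost, or that power will fall from 82% to 63%.** The first range holds only for a normal score cut somewhere between the median and 10/90. The second assumes a 0.25 SD effect found nowhere in the article and uses 265 per arm without the design effect. At 92 per group, power for 0.25 SD is about 40% even with no cut: 0.25 × √46 − 1.960 = −0.264, and Φ(−0.264) ≈ 0.40.

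The reply does not remove the mismatch itself. The article did not leave the adjusted model to another document. It named one and applied it to every outcome, including several for which it is unsuitable.

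**Conclusion.** The point holds in a limited form. The one adjusted model named does not fit the continuous, scale-score and ordinal outcomes within its stated scope. If it were followed literally for a normal score, a median split would cost about 36% of the information, and power for a 0.41 SD difference at 92 per group would fall from 80% to about 60%; more extreme cuts would cost more. These figures are conditional on normality, on the assumed cut and on the article's own design effect of 2.9.

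The reach is restricted. The main GEE analysis is unaffected. The Table 2 prevalences, which the article treats as primary, are suited to logistic regression and keep their stated power. The adjustment arises only if baseline imbalance is noted. This is a correction to the adjusted analysis of the other outcomes and does not undermine the trial's main comparison.

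**What to change.** Replace the adjustment sentence with one that says:

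- all adjusted effects are estimated within the same GEE framework as the main analysis, clustered on assessment clinic;
- the logistic (binomial, logit-link) model is used for binary outcomes only, such as the Table 2 prevalences;
- z-scores and scale scores are analysed undichotomised with an identity link, giving adjusted mean differences;
- 5-point preference ratings are analysed with an ordinal or other suitable model, named in advance.

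If a cut is wanted for interpretation, its value and rationale should be fixed before the data are examined and the result presented as supplementary.

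The cost is an edit to one sentence. No further data, visits or participants are needed, and the GEE framework already chosen accommodates the binary and continuous models.
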